### Statistical methods

Data will be analysed using SPSS software (Version 17.0; SPSS Inc; Chi). Data that are not normally distributed will be transformed and if transformation fails to satisfy normality, non-parametric tests will be used. The primary and secondary outcomes in the exercise and control groups will be compared using two-way analysis of variance to account for group and time interactions. Statistical relationships between outcome variables will be analysed using Pearson's or Spearman's correlations as appropriate. Data will be analysed using (i) per protocol analysis and (ii) intention-to-treat analysis. Per protocol analysis will be restricted to the data from subjects who complete all assessments and for the exercise group who attend at least 75% of their exercise classes. The required number of sessions must be achieved within a period of 15 weeks for both the supervised and home exercise training programs, allowing for intercurrent illness and other factors that may impact on an individual's ability to attend sessions. The last-observation-carried-forward method will be used to impute missing data at 12 and 24 weeks for the intention-to-treat analysis [41]. The Berger-Exner [42] test will be carried out to determine whether selection bias has been introduced into the study.

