### Withdrawal Criteria

Subjects will be withdrawn from the study if they demonstrate deterioration in their clinical status (time to clinical worsening), defined by the presence of two or more of the following [38,39]: (i) escalation of medical therapy (increased dose of medication or commencement of intravenous epoprostenol); (ii) deterioration (≥ 1) in WHO functional class; (iii) development of right heart failure (as indicated by increased jugular venous pressure, new/worsening hepatomegaly, ascites or peripheral oedema); (iv) resting echocardiogram changes (deterioration in right ventricular size and function, right atrial size, pulmonary arterial systolic pressure (PASP) and, where PASP cannot be determined, pulmonary acceleration time); (v) oedema that does not respond to oral diuretics; (vi) hospitalisation for PAH; (vii) listing for transplantation; (viii) ≥ 20% deterioration in 6MWD (ix) progressive worsening of dyspnoea at rest or on exertion over the past 3-5 days [40]; (x) deterioration in ventilatory efficiency (V_E_/VCO_2_) reflecting worsening gas exchange.

Subjects may also be withdrawn from the study at their request or if they experience a serious adverse event during or up to 24 hours following an exercise training session and it is deemed unsafe to continue participation by the treating medical officer from the Royal Perth Hospital Pulmonary Hypertension Service. Adverse events comprise: (i) an incident requiring a medical emergency team call (according to Royal Perth Hospital criteria); (ii) exercise-related incident requiring presentation to the Emergency Department or General Practitioner; (iii) hospital admission due to PAH or worsening right heart failure; (iv) an incident resulting in the patient ceasing exercise during class (chest pain, syncope, worsening dyspnoea despite rests, hypotension/hypertension, bradycardia/tachycardia (as measured by a polar monitor and confirmed by palpation), nausea (associated with sweating, pallor and/or tremor), vagueness, vasovagal, arrhythmia); (v) death.

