### Outcomes

The primary outcomes of this study will be:

(i) Peak VO_2_;

(ii) Anaerobic threshold;

(iii) Endurance time measured from the constant workload cycle ergometry test;

(iv) HRQoL measured using the CAMPHOR and SF 36 Version 2;

(v) The number of reported acute adverse events (i) reported during exercise training and (ii) resulting in the withdrawal of a subject from the study.

The secondary outcomes of this study will be:

(i) Ventilatory variables at isotime during the constant workload cycle ergometry test (ventilatory equivalent for carbon dioxide [VE/VCO_2_] and end tidal carbon dioxide [PetCO_2_] to describe gas exchange);

(ii) Change in WHO functional class;

(iii) 6MWD (measured from the best of two 6MWTs at each assessment);

(iv) Worsening clinical status (see withdrawal criteria).

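### Clinical worsening, a once-only event that ends participation, is assigned with all other outcomes to a group-by-time ANOVA, and the analysis sets can lose or mask it

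*Protocol article*

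**What the plan says.** Four parts of the protocol article bear on this point.

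- **Statistical methods, main comparison.** "The primary and secondary outcomes in the exercise and control groups will be compared using two-way analysis of variance". The stated purpose is to handle group-by-time interaction. No outcome is exempted, and the article names no time-to-event or proportion method.
- **Statistical methods, fallback.** "Data that are not normally distributed will be transformed and if transformation fails to satisfy normality, non-parametric tests will be used".
- **Outcomes.** Secondary outcome (ii) is "Change in WHO functional class". Secondary outcome (iv) is "Worsening clinical status (see withdrawal criteria").
- **Withdrawal Criteria.** "Subjects will be withdrawn from the study if they demonstrate deterioration in their clinical status (time to clinical worsening"), with deterioration "defined by the presence of two or more of the following", a list of ten components. One component is a fall of at least one WHO functional class.

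The Statistical methods section also sets the analysis populations. The per protocol set keeps only subjects who complete every assessment and, in the exercise group, reach the attendance threshold. In the intention-to-treat analysis, missing values at 12 and 24 weeks are filled by LOCF.

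**The concern.** A group-by-time ANOVA compares mean profiles of a response measured at baseline, 12 and 24 weeks. Clinical worsening is not such a response. Everyone is free of it at baseline, it can happen once, and it ends participation, so nothing need be measured afterwards. No transformation makes a yes/no variable normal. The non-parametric fallback reduces it to a comparison of proportions and takes no account of when subjects worsened or how long the others were observed.

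The analysis sets make this worse. The event is itself a reason for leaving the per protocol set. In the intention-to-treat analysis, the value carried forward may predate the deterioration.

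Hypothesis (ii) in the Background says that gains will come without evidence of clinical worsening. The other harm outcome, primary outcome (v), counts adverse events during exercise training, which have no counterpart in the control group, and adverse events leading to withdrawal. Outcome (iv) is therefore the main randomised comparison of worsening.

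**Working it through.** **Inputs.** 17 subjects per arm (Sample size calculation); assessments at baseline, 12 and 24 weeks (Recruitment and Randomisation); entry in WHO class II or III (Inclusion/Exclusion Criteria). The article gives no expected rate of worsening and no power for it, so there is no figure of its own to reproduce. All event counts and risks below are assumptions.

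**1. Per protocol set.** Suppose 4 of 17 exercise subjects and 0 of 17 controls worsen and are withdrawn before the 24-week assessment. The risk difference among all randomised subjects is 4/17 − 0/17 = 23.5 percentage points. The four have not completed all assessments, so the per protocol comparison is at most 0/13 against 0/17, a difference of 0. Only worsening first established at the 24-week assessment can survive in that set.

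**2. LOCF and WHO class.** Take a subject in class II at baseline who moves to class III and is withdrawn before week 12 without a further scheduled assessment. The true change is +1. LOCF puts class II at weeks 12 and 24, a change of 0.

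**3. What the ANOVA does with timing.** Code worsened status as 0 at baseline and 0/1 at weeks 12 and 24, and keep it at 1 after the event. With 4 against 0 of 17, the interaction F has 2 and 64 degrees of freedom.

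- All four events before week 12, or all four between weeks 12 and 24: interaction sum of squares 0.3137, error sum of squares 2.0392. F = (0.3137/2)/(2.0392/64) = 4.92, P = 0.010 in both cases.
- Two events in each period: 0.2353 and 2.1961. F = (0.2353/2)/(2.1961/64) = 3.43, P = 0.039.

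The model can be fitted, but it gives the same P for all-early and all-late worsening, and a different P for the same total spread over both periods.

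**4. Single-time tests on the same kind of table.** For 4 against 0 of 17:

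- t-test (ANOVA on two groups): variance in the exercise arm 0.2353 × 0.7647 × 17/16 = 0.1912, pooled 0.0956; t = 0.2353/√(0.0956 × 2/17) = 2.22 on 32 degrees of freedom.
- Fisher: 2 × C(17,4)/C(34,4) = 2 × 2380/46376 = 0.103.

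| Worsened | t-test | Rank test, large-sample | Fisher | Barnard | Boschloo |
|---|---|---|---|---|---|
| 4/17 v 0/17 | 0.034 | 0.036 | 0.103 | 0.036 | 0.058 |
| 6/17 v 1/17 | 0.034 | 0.037 | 0.085 | 0.046 | 0.058 |
| 4/14 v 0/14 | 0.031 | 0.034 | 0.098 | 0.042 | 0.042 |

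**5. Type I error at nominal two-sided 0.05, 17 per arm.** The t, rank and Fisher columns are exact binomial enumeration. The group-by-time column is simulation (100,000 runs) on the 0/1 status of step 3.

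| Common risk | t and rank test | Fisher | Group-by-time ANOVA |
|---|---|---|---|
| 5% | 0.007 | 0.001 | 0.017 |
| 10% | 0.031 | 0.008 | 0.046 |
| 20% | 0.046 | 0.019 | 0.061 |
| 30% | 0.046 | 0.020 | 0.056 |

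At nominal 0.01, the level used for the sample size, the simulated ANOVA gave 0.001, 0.004, 0.012 and 0.014. For simulated WHO class scores at nominal 0.05 it gave 0.057 to 0.058.

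**6. Power, 17 per arm, two-sided 0.05.** For 10% against 30%: Fisher 0.19; t, rank and chi-square tests 0.30. For 10% against 40%: 0.39 and 0.53.

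**The case against.** A reader might infer that the ANOVA cannot test these outcomes, that the comparison of harm is invalid, or that planned and valid methods would reach opposite conclusions. The documents and the figures do not support this. The model can be fitted, and its type I error stays close to or below nominal. The contrast with Fisher's test comes from Fisher's conservatism: its true size here is at most two-fifths of nominal. Barnard's test, also exact, falls on the same side of 0.05 as the planned methods in all three tables.

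Three further objections carry weight.

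- **WHO class.** The fallback leads to a rank test for an ordinal score with few values, which largely meets the need. What remains for this outcome is mainly the carried-forward value.
- **Timing.** The Outcomes section lists worsening status; the time label is only a parenthesis in the Withdrawal Criteria. Some components, such as walk distance and ventilatory efficiency, come from tests scheduled at baseline, 12 and 24 weeks, so many onset dates may be tied at visits. This argues for the 24-week risk as the main measure, with time-to-event analysis as support.
- **Hypothesis (ii).** It also draws on primary outcome (v), and no single between-group test is made decisive.

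None of this answers the per protocol exclusion or the masking by LOCF. An unseen analysis plan might name a better method, but the rule published here is explicit and makes no exception.

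**Conclusion.** The point holds as a mismatch between outcome and method, not as a finding of invalid inference. Following the published rule would put a once-only event through a mean-profile model that does not represent its timing or censoring, remove subjects withdrawn for worsening before completion from the per protocol set, and allow a pre-worsening WHO class to stand as no change. In the illustration, a 23.5-point risk difference disappears entirely from the per protocol comparison.

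There is no evidence of material type I error inflation: the highest simulated value was 0.061 at nominal 0.05. These figures rest on assumed risks of 5% to 30%, equal observation in both arms and, for the ANOVA, worsened status kept at 1 after the event. Low power at 17 per arm limits any method.

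**What to change.** In the Statistical methods section:

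- Limit ANOVA to continuous outcomes.
- Analyse worsening in all randomised subjects as a first event by 24 weeks. Report the risk difference with an exact unconditional interval and test. Name one test, Barnard or Boschloo, in advance, since they fall on different sides of 0.05 in two of the three tables above. Add Kaplan-Meier curves and a permutation log-rank test as support.
- Do not treat withdrawals for session-related serious adverse events as uninformative censoring. Under the Withdrawal Criteria they can arise only in subjects who attend training, so censoring them would favour the exercise arm if those subjects are the ones likely to worsen. Report them alongside, with a sensitivity analysis that counts them as events.
- Analyse WHO class with an ordinal or rank method, using the class recorded at worsening in place of LOCF from an earlier visit.

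The cost is revised analysis wording and a little more analysis work. It also requires the date of worsening and the WHO class at that time to be recorded. It does not cure the low power when events are few, so the interval should carry the interpretation.

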The studies to date have demonstrated improvements in exercise capacity in this patient population [10,15,25], however these studies have some limitations in the application of exercise training in Australia. Uchi et al [25] recruited subjects who had recently commenced intravenous PAH therapy and thus it is not possible to differentiate between the benefits of exercise and those attributed to the medication. The training programs have included a variety of modalities such as mental training and yoga [15], interventions that do not form part of most cardiopulmonary rehabilitation programs. Within Australia, most rehabilitation programs designed for cardiac or respiratory populations consist of whole body exercise training and take place in hospital outpatient departments or in community settings [26,27]. This contrasts with the study by Mereles et al [15] in which subjects were admitted for a 3 week inpatient training program prior to performing a 12 week home exercise program. In Australia, the resources for providing inpatient exercise training to individuals who are stable on medical therapy are limited [24]. The study by de Man et al [10] evaluated a 12 week outpatient exercise training program which comprised cycling and quadriceps training. The specificity of lower limb exercise training in this study is likely to account for the large increase in endurance cycle time and may explain the non-significant improvement in 6MWD.

To date, the studies have only reported the immediate effects of exercise training and thus it remains unknown whether the benefits are maintained following cessation of supervised training. It is also unknown whether an outpatient-based, whole body exercise training program is beneficial in patients with PAH and whether this type of program is capable of producing sustained benefits in exercise capacity and HRQoL.

This study aims to investigate the benefits of a 12 week hospital outpatient-based, individualised exercise training program involving supervised exercise sessions, followed by a 12 week home exercise program, for a cohort of subjects with PAH.

We hypothesise that:

(i) A 12 week individualised, whole body exercise training program will improve:

• Exercise capacity (as assessed by peak VO_2_; anaerobic threshold; endurance time measured during the constant-workload cycle ergometry test)

• HRQoL

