(ii) Exercise training is safe and improvements in exercise capacity will be achieved without evidence of clinical worsening

(iii) An additional 12 week home exercise program will maintain or further improve the benefits gained during the 12 week, supervised, outpatient program.

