**Figure 1 F1:**
[figure not shown]
Study design

All subjects will undergo a baseline assessment and re-assessment at 12 and 24 weeks. Following baseline assessment, stratified randomisation to the exercise or control group will be performed. Permuted block randomisation with block sizes of 4 will be used [29]. In order to achieve groups balanced for exercise capacity, subjects will be stratified based on the peak VO_2 _> or ≤ 70% of predicted values [30].

Subjects in both groups will receive usual medical care. Subjects randomised to the exercise group will undergo a 12 week, individually prescribed, supervised, outpatient exercise training program, followed by a 12 week home exercise program.

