### Sample size calculation

Improvements in endurance time following exercise training have recently been reported in the PAH population [10]. These authors [10] reported a mean increase in endurance time, as measured from a constant workload cycle ergometer test, of 270 seconds. The constant workload tests were set at 75% of the peak workload achieved during the incremental CPET, which is consistent with our study's protocol. The mean endurance time (standard deviation) at baseline and post-training were 390 (40) and 660 (60) seconds respectively.

Conservative sample size calculations have been performed using a two-sided Mann-Whitney U test, assuming that the actual distribution is a double exponential. Group sizes of 14 will achieve 91% power to detect a difference of 200 seconds between the null hypothesis that both group means are 600 seconds and the alternative hypothesis that the mean of group 2 is 400 seconds with estimated group standard deviations of 180 and 120 and with a significance level (alpha) of 0.01.

A total of 34 subjects (17 in the exercise group and 17 controls) will be recruited to allow for 20% attrition of subjects from the per protocol analysis.

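### The group-by-time ANOVA is an omnibus test that isolates neither the 12-week nor the 24-week effect, and it is also assigned to event outcomes it does not suit

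*Protocol article*

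**What the plan says.** Statistical methods gives a single sentence on the between-group comparison. Its subject is every primary and secondary outcome, and these "will be compared using two-way analysis of variance to account for group and time interactions". Before it comes a general fallback: data that are not normal are transformed, and if that fails, non-parametric tests are used. No visit-specific contrast, baseline covariate or stratum term is mentioned, and the visits are not described as repeated measures.

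The rest of the article sets what this test has to answer:

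- **Visits** (Recruitment and Randomisation, text under Figure 1): "All subjects will undergo a baseline assessment and re-assessment at 12 and 24 weeks".
- **Hypothesis (i)** (Background): "A 12 week individualised, whole body exercise training program will improve" exercise capacity and quality of life.
- **Hypothesis (iii)** (Background): "An additional 12 week home exercise program will maintain or further improve the benefits gained during the 12 week, supervised, outpatient program".
- **Stratification** (text under Figure 1): "In order to achieve groups balanced for exercise capacity, subjects will be stratified based on the peak" VO2, cut at 70% of predicted.
- **Outcomes**: besides continuous measures, the primary list includes counts of adverse events during training and of those leading to withdrawal. The secondary list includes "Change in WHO functional class" and worsening clinical status.
- **Sample size calculation**: power was computed "using a two-sided Mann-Whitney U test, assuming that the actual distribution is a double exponential", which is a comparison of single values in two groups.

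**The concern.** The hypotheses are tied to time: one concerns the gain at 12 weeks, the other whether the gain holds to 24 weeks. If all three visits are levels of time, which is the natural reading, the interaction asks only whether the group difference varies somewhere across the visits. A significant result would be consistent with a lasting gain, with a gain that has vanished by 24 weeks, or with one that appears only late.

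Two further matters follow. With 34 subjects, the efficiency with which baseline is used counts, and the variable chosen for balancing the groups does not appear in the stated analysis. The sentence also reaches outcomes with no group-by-time structure. Events during training cannot occur in a control group that does no training, and clinical worsening is an event that leads to withdrawal, not a value measured at each visit. One of these is a primary safety outcome.

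**Working it through.** **1. The plan's own figure.** Inputs (Sample size calculation): 14 per group, means 600 and 400 s, SDs 180 and 120 s, two-sided alpha 0.01, stated power 91%. For a double exponential the Mann-Whitney test has asymptotic efficiency 1.5 relative to the t test, so 14 per group acts like 14 × 1.5 = 21. The noncentrality is 200 / √(180²/21 + 120²/21) = 4.24 on 34.8 Welch degrees of freedom, and power is 92.7%. An effective size of 20 gives 91.1%. The stated 91% reproduces within two points, but it belongs to a two-group comparison of single values, not to the interaction.

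**2. Inputs for the comparison of methods.** Common variance (180² + 120²)/2 = 23,400, so SD 153 s; 14 per group; alpha 0.01; effect 200 s at 12 weeks. The within-subject correlation ρ is not in the article. I assume 0.3 to 0.8 with compound symmetry. These are normal-theory powers without the factor 1.5, so they should be compared with each other and not with 91%.

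**3. What the interaction can distinguish.** Noncentrality λ = (n/2) × Σd² / [σ²(1 − ρ)], where d is the group difference at each visit minus its mean over the three visits.

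- Effect at both follow-ups (0, 200, 200): d = −133.3, 66.7, 66.7; Σd² = 26,667.
- Effect at 12 weeks only (0, 200, 0): d = −66.7, 133.3, −66.7; Σd² = 26,667.
- Effect at 24 weeks only (0, 0, 200): Σd² = 26,667.
- Effect halved by 24 weeks (0, 200, 100): d = −100, 100, 0; Σd² = 20,000.

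The first three patterns give the same λ. At ρ = 0.5, λ = 7 × 26,667 / (23,400 × 0.5) = 15.95. Against F(2, 52) with critical value 5.04, power is 82.4% in all three cases.

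**4. 12-week ANCOVA.** Noncentrality = 200 / √[2 × 23,400 × (1 − ρ²)/14] on 25 degrees of freedom, critical t 2.787. At ρ = 0.5 this is 200 / 50.07 = 3.99, and power is 87.5%.

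| ρ (assumed) | 12-week ANCOVA | Interaction, effect sustained | Interaction, effect halved by 24 weeks |
|---|---|---|---|
| 0.3 | 79.0% | 63.9% | 47.5% |
| 0.5 | 87.5% | 82.4% | 66.8% |
| 0.7 | 97.4% | 97.8% | 91.5% |
| 0.8 | 99.7% | 99.9% | 99.0% |

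The loss against ANCOVA with a sustained effect is about 15 points at ρ = 0.3, 5 at 0.5 and none at 0.7 or above. With the effect halved it is about 32, 21, 6 and 1 points.

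**5. Use of baseline.** For one follow-up visit, a comparison of changes has variance 2(1 − ρ)σ² per subject, and ANCOVA has (1 − ρ²)σ². The ratio is (1 + ρ)/2: 0.65, 0.75, 0.85 and 0.90 at the four correlations. The interaction catches up at high ρ because the 24-week data add evidence, which is also why it is not a 12-week test.

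**6. Stratum.** The article gives no association between stratum and outcome, so the gain from including it cannot be computed.

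**7. Outcomes set beside the method.** Training-related events exist only in the exercise group and have no baseline value. Clinical worsening is a withdrawal event. WHO class is ordinal, with entry limited to classes II and III. The transform-or-non-parametric fallback could lead to a rank test for WHO class, but it names nothing for counts or events.

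**The case against.** The strongest reply is that this is one paragraph of a condensed article, and that visit-specific contrasts, covariates and covariance form are commonly left to an analysis plan, which is not shown. That stands for the omissions as such: the missing stratum term alone would be weak evidence of a fault. It does not remove the mismatch between the one test that is named and the hypotheses it is meant to answer, nor the assignment of that test to every outcome.

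Three stronger readings are tempting, and the article does not support them.

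- *Baseline is ignored.* If baseline is a level of time, the interaction compares changes from baseline. Baseline is used, though less efficiently than as a covariate.
- *The ANOVA always gives away power.* At ρ of 0.7 or above with a sustained effect, the interaction does as well as a 12-week ANCOVA.
- *The visits would be analysed as independent, so error rates would be wrong.* The wording does not say repeated measures, but it does not say independence either. A group-by-time ANOVA on scheduled reassessments is usual shorthand for the repeated-measures form. The wording needs clarifying; miscalibration cannot be presumed.

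It is also fair to say that the fallback may already give WHO class a suitable test.

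**Conclusion.** The point holds with limits. The named interaction test does not isolate the 12-week effect and cannot tell a sustained gain from one lost by 24 weeks; this part needs only the three visits as levels of time, which is inferred from the visit schedule. The power cost depends on the assumed correlation and on whether the effect lasts: clear at ρ of about 0.5 or below or if the effect wanes, absent at 0.7 or above if it is sustained. Those figures rest on compound symmetry, a common SD of 153 s and the planned 200 s. The method is also unsuited to adverse-event counts and clinical worsening. This is a should-fix matter: a better-matched analysis is available from data already collected, and nothing shows that the planned test, in its repeated-measures form, is invalid for the continuous outcomes.

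**What to change.** For continuous outcomes, replace the sentence with a mixed model for repeated measures, or ANCOVA, of the follow-up values on group × visit, baseline × visit and the peak VO2 stratum. State explicitly that visits are repeated measures within subject. Name the 12-week group contrast first and the 24-week contrast second. For WHO class, specify a rank or proportional-odds method. For adverse events and clinical worsening, specify exact or descriptive methods, with training-related events reported for the exercise group alone.

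The cost is analysis wording only, plus one or two degrees of freedom for covariates. Baseline values and the stratum are already collected, and neither the visit schedule nor the recruitment target changes.

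### The per-protocol analysis is not limited to efficacy, so adverse events causing withdrawal are zero there by construction, and clinical worsening and training-related events are biased towards zero

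*Protocol article*

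**What the plan says.** All references are to the protocol article.

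- **Scope of the analysis (Statistical methods).** "The primary and secondary outcomes in the exercise and control groups will be compared using two-way analysis of variance", and "Data will be analysed using (i) per protocol analysis and (ii) intention-to-treat analysis". No outcome is exempted from either analysis.
- **Per-protocol set (Statistical methods).** "Per protocol analysis will be restricted to the data from subjects who complete all assessments"; exercise-group subjects must in addition have attended at least 75% of their classes. The assessments are those at baseline, 12 and 24 weeks (Recruitment and Randomisation, text beside Figure 1): "All subjects will undergo a baseline assessment and re-assessment at 12 and 24 weeks".
- **Safety outcomes (Outcomes).** Primary outcome (v) is the number of acute adverse events, in two components: (i) those reported during exercise training and (ii) those "resulting in the withdrawal of a subject from the study". Secondary outcome (iv) is "Worsening clinical status (see withdrawal criteria").
- **Link between event and withdrawal (Withdrawal Criteria).** "Subjects will be withdrawn from the study if they demonstrate deterioration in their clinical status (time to clinical worsening"), where deterioration means that two or more listed criteria are present. A subject may also be withdrawn after a serious adverse event during training, or within 24 hours of it, if continuing is judged unsafe.
- **Missing data (Statistical methods).** For the intention-to-treat analysis, missing values at 12 and 24 weeks are filled by last observation carried forward.

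**The concern.** An analysis set should not be defined by the outcome that it is used to measure. Here, two safety outcomes are tied to leaving the study, and one of the two analysis sets admits only subjects who stayed to the end. For adverse events causing withdrawal, the per-protocol analysis can return only one answer.

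Safety is one of the trial's stated questions. Hypothesis (ii) in the Background is that training is safe and that gains come without clinical worsening. The Discussion says that adverse events and worsening are monitored to address concerns about harm, and that the trial will inform practice guidelines. A per-protocol table with no withdrawals for adverse events would look like evidence for that hypothesis but would carry no information about it.

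The attendance rule adds a filter in the exercise group alone. A subject who stops attending because of an event in class may fall below 75% attendance and leave the set, taking that event out of component (i). Controls face no such filter.

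**Working it through.** **Step 1. Follow each safety outcome into the per-protocol set.** This assumes that withdrawal from the study ends the assessments. The article does not say otherwise, and it plans imputation at 12 and 24 weeks.

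| Outcome | Subject with the event | In the per-protocol set? | Per-protocol count |
|---|---|---|---|
| (v)(ii) adverse event causing withdrawal | Leaves before completing the 24-week assessment | Never | Zero by construction |
| Secondary (iv), worsening met before the 24-week assessment | Withdrawn | No | Lost |
| Secondary (iv), worsening first met at the 24-week assessment | Can have completed everything | Yes, if the attendance rule is met | Counted |
| (v)(i) adverse event during training | May continue, stop attending or be withdrawn | Only if the subject continues and attends enough | Undercounted |

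The third row arises because some worsening criteria, such as a 20% fall in 6-minute walk distance or a deterioration in ventilatory efficiency, are measured at the assessment visits.

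**Step 2. The plan's own figures.** No safety rate is stated, so there is none to reproduce. The Sample size calculation section gives 17 per group recruited, 14 per group needed and 20% attrition from the per-protocol analysis: 17 × 0.8 = 13.6, or about 14. The implied loss is about 3 per group.

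**Step 3. Illustration for (v)(ii).** Assume that 1, 2 or 3 of 17 exercise subjects are withdrawn for an adverse event. Intervals are exact (Clopper-Pearson) 95%.

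| Withdrawn | All randomised | Per protocol |
|---|---|---|
| 1 | 1/17 = 5.9% (0.1 to 28.7) | 0 events |
| 2 | 2/17 = 11.8% (1.5 to 36.4) | 0 events |
| 3 | 3/17 = 17.6% (3.8 to 43.4) | 0/14 = 0% (0 to 23.2) |

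The last row treats all attrition in the exercise group as safety withdrawal.

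If w is an assumed true withdrawal probability, the chance of at least one such event among 17 is 1 − (1 − w)^17:

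- w = 5%: 17 × 0.05 = 0.85 expected; chance of at least one 58%
- w = 10%: 1.7 expected; 83%
- w = 20%: 3.4 expected; 98%

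The per-protocol count is 0 in every case.

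**Step 4. Illustration for worsening.** Assume a total risk of 20% in an arm of 17, and let s be the share of cases first detected at the 24-week assessment. Ignoring other exclusions, the expected per-protocol count is 17 × 0.2 × s, and the chance of no per-protocol case is (1 − 0.2s)^17. Over all randomised subjects, 17 × 0.2 = 3.4 cases are expected.

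| s | Expected per-protocol count | Chance of no per-protocol case |
|---|---|---|
| 0% | 0 | 100% |
| 10% | 0.34 | 71% |
| 25% | 0.85 | 42% |
| 50% | 1.70 | 17% |

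The count falls short of 3.4 throughout, but it is not necessarily zero. The article does not give s.

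**The case against.** The strongest reply is that the same section also plans an intention-to-treat analysis, which keeps every withdrawn subject. The contrast of 3/17 with 0/14 is in effect one planned analysis set against the other, and the trial would report both. This stands, and it limits the point to one of two analyses.

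A reader might infer that the per-protocol result governs safety, because it is listed first and the sample size allows for attrition from it. The documents do not support that. List order is not a declared hierarchy, and the sample size concerns endurance time only. A reader might also infer that worsening would almost always be zero per protocol. That is not supported either: cases first met at 24 weeks can remain, and Step 4 shows that a non-zero count is quite possible.

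It can also be said that no sentence expressly assigns adverse-event counts to the per-protocol set. Events during training have no counterpart among controls, so the two-way analysis of variance cannot literally apply to every listed outcome, and the wording may simply be condensed. This is fair as an account of how the text arose. But the article does more than stay silent: it states a general rule and a set definition, and together these give an uninformative result on a named primary outcome.

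Finally, the 20% attrition covers any reason, including low attendance and subject request. The figures in Step 3 are therefore illustrations, and the 0/14 interval itself contains 17.6%. That also stands.

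The intention-to-treat analysis does not settle everything. Its only stated missing-data rule is last observation carried forward. Read literally for worsening, that rule could carry forward a status from before the event unless the withdrawal itself is counted.

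**Conclusion.** The point holds in limited form. As written, the per-protocol analysis covers the safety outcomes. In that set, adverse events causing withdrawal are zero at any true rate, on the reading that withdrawn subjects do not complete later assessments. Worsening clinical status and adverse events during training are biased towards zero. The size of that bias depends on when worsening is detected and on how events affect attendance, and the article gives neither.

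The conclusion does not extend to the safety assessment as a whole, because the intention-to-treat analysis retains these subjects. Nor does the article support any particular rate of safety withdrawal. What needs correcting is a stated rule that yields an uninformative result on one component of a primary outcome and an understated one on two others.

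**What to change.** In Statistical methods:

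- Limit the per-protocol analysis to efficacy outcomes.
- Report primary outcome (v) and secondary outcome (iv) in all randomised subjects. For training-related events, use all exercise-group subjects who started training as the denominator.
- Count events as observed, up to and including the one that causes withdrawal, and not by last observation carried forward.
- Present numbers of subjects with exact confidence intervals.

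This takes about one sentence and needs no extra subjects or data. The downside is that the reported safety rates may look less favourable than those in a completers-only table.
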